## Abstract

**Background:**

Recent evidence suggests that frequent monitoring using smartphone-compatible wearable technologies might improve clinical effectiveness and patient satisfaction of care.

**Objective:**

The aim of this study is to investigate the clinical effectiveness and patient satisfaction of a smart technology intervention in patients admitted with a ST elevation myocardial infarction (STEMI) or non-ST acute coronary syndrome (NST-ACS).

**Methods:**

In this single center, open, randomized controlled trial patients who suffered from STEMI or NST-ACS will be randomized 1:1 to an intervention group or control group. Both groups will be followed up to one year after the index event. The intervention group will take daily measurements with a smartphone-compatible electrocardiogram device, blood pressure (BP) monitor, weight scale, and activity tracker. Furthermore, two of four outpatient clinic visits will be replaced by electronic visits (1 and 6 months after index event). The control group will receive regular care, consisting of four outpatient clinic visits (1, 3, 6, and 12 months after index event). All patients will be asked to fill in validated questionnaires about patient satisfaction, quality of life, propensity of medication adherence, and physical activity.

**Results:**

The primary outcome of this trial will be percentage of patients with controlled BP. Secondary outcomes include patient satisfaction, health care utilization, major adverse cardiac events, medication adherence, physical activity, quality of life, and percentage of patients in which a sustained arrhythmia is detected.

**Conclusions:**

Smart technology could potentially improve care in postmyocardial infarction patients. This trial will investigate whether usage of smart technology can improve clinical- and cost-effectiveness of care.

**Trial Registration:**

Clinicaltrials.gov NCT02976376; https://clinicaltrials.gov/ct2/show/NCT02976376 (Archived by WebCite at http://www.webcitation.org/6tcvAdbdH)

## Introduction

Current European Society of Cardiology guidelines on secondary prevention in patients with sustained ST elevation myocardial infarction (STEMI) or acute coronary syndrome without persistent ST elevation (non-ST acute coronary syndrome; NST-ACS) recommend tight blood pressure (BP) control, weight control, and adequate physical activity after discharge from the hospital, as well as regular electrocardiograms (ECGs) [1,2]. In current practice, these patients regularly visit outpatient clinics in the first year after their initial hospitalization, where the patient is interviewed, weighed, an ECG is recorded, BP is measured, lifestyle advices are given, and pharmaceutical treatment is evaluated [3]. In this situation, patients must be physically present at the outpatient clinic [3], which might pose a burden to the patient, especially in remote areas [4]. Furthermore, this process necessitates trained health care staff, which increases their workload.

Recent advances in information and communication technologies have enabled remote monitoring of vital signs and remote doctor-patient contacts (together encompassing part of the broad concept of *telemedicine*) [5-9]. In recent years, a number of smartphone-compatible wearables have received a European Conformity (CE)-mark and Food and Drug Administration (FDA) clearance, and are available for over-the-counter sale in the European Union and the United States [10]. Some of these smartphone-compatible wearables allow for the measurement of (depending on the type of wearable) the number of steps taken per day, BP, weight, and the recording of an ECG. The devices are easy-to-use and do not require the assistance of trained health care staff. Results of measurements are communicated with smartphone apps tailored to the specific device. Data is uploaded via the Internet to servers belonging to the manufacturers of the devices [10,11].

Recent research in various patient populations suggests that telemedicine might improve clinical effectiveness and patient satisfaction of care [12,13]. Remote and more frequent monitoring with subsequent therapy changes has been shown to improve clinical outcomes of patients with uncontrolled hypertension (achieving 18.4% more patients with controlled BP) [12] and with type 2 diabetes mellitus (a statistically significant 0.37% reduction in hemoglobin A1c) [13]. Furthermore, remote video contact moments, in which the doctor and patient communicate via a video connection, are potentially time-saving for patients [14,15]. One study found that office visits required an average of 50 minutes of a patient’s time, while electronic visits only required 22 minutes on average [15].

We therefore hypothesize that telemedicine improves clinical effectiveness and patient satisfaction of care in the follow-up of STEMI and NST-ACS patients. Thus, the aim of this study is to investigate the clinical effectiveness and patient satisfaction of a smart technology intervention in patients after being admitted with a STEMI or NST-ACS. In this paper, the rationale and design of this open, single center, randomized controlled trial (RCT) are presented.

## Methods

### Study Design (Design, Randomization, and Follow-Up)

*The Box* is a single-center open RCT, and is a parallel group study. The study will be conducted at the Leiden University Medical Center (LUMC), a tertiary care hospital in Leiden, The Netherlands. The trial is registered under clinical trial number NCT02976376 (Clinicaltrials.gov) and NL56453.058.16 (Toetsingonline.nl). After inclusion, patients will be randomized 1:1 to either *The Box* (intervention group) or to regular follow-up (control group). Block randomization per 10 participants will be performed. Randomization will be stratified per primary diagnosis (STEMI or NST-ACS) and per age (<50, 51-60, 61-70, 71-80, and >80 years). A website will be used to generate randomization lists [16].

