### Statistical Analyses

A power calculation was done using R software [24], which is based on a comparison of two proportions of patients with controlled BP (defined as an SBP of 139 mmHg or less and a DBP of 89 mmHg or less). We hypothesize that in the *The Box* group, 95% of the patients will achieve controlled BP, while in the control group, 75% will achieve controlled BP [25]. For this calculation, an alpha of 0.05, a beta of 0.20, and a margin of 0.07 were chosen, yielding a sample size of 200 patients.

Data will be analyzed according to the intention-to-treat principle. Causes of missing data will be tabulated (Multimedia Appendix 1). The percentage of missing data is expected to be low. Therefore, complete case analyses will be done. Analyses will be based on the missing-at-random assumption. If the percentage of missing values exceeds 7%, multiple imputation will be applied in the analysis of the data.

After finishing the study (defined as the last patient’s last visit), the proportion of patients with controlled BP will be compared with a Chi-square test. Logistic regression might be done if serious imbalances of baseline variables exist, to correct for potential confounding variables. Percentages of patients with controlled BP at three months (secondary outcome 1), and percentages of patients in which a previously unknown sustained arrhythmia is detected, will also be compared with a Chi-square test.

Scores of questionnaires (patient satisfaction questionnaire, MMAS-8 scale, iPAQ questionnaire, and SF-36 questionnaire) and health care utilization will be compared using an independent t-test. Major Adverse Cardiac Events (MACEs) will only be reported. As the study is underpowered, no statistics will be done on MACEs. The numbers will be hypothesis-generating.

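### Two separate faults in the randomisation rule: no age stratum for a patient aged exactly 50, and one published block size of 10 that makes block ends deducible in an open single-centre trial

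*Protocol article*

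**What the plan says.** All the relevant text is in the protocol article, under Study Design (Design, Randomization, and Follow-Up), unless noted.

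- Setting: the trial "is a single-center open RCT, and is a parallel group study".
- Order and ratio: "After inclusion, patients will be randomized 1:1".
- Blocks: "Block randomization per 10 participants will be performed". No other size is mentioned.
- Strata: "Randomization will be stratified per primary diagnosis (STEMI or NST-ACS") and "per age (<50, 51-60, 61-70, 71-80, and >80 years").
- Source of allocations: "A website will be used to generate randomization lists".
- Size: the Statistical Analyses section gives a power calculation "yielding a sample size of 200 patients".

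The only age limit in the eligibility textbox (Patient Population) is the exclusion of patients under 18, so a 50-year-old can enter. The article does not say who holds the lists or how the next allocation is released.

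**The concern.** **Age 50.** The first age class stops below 50 and the second starts at 51. A 50-year-old therefore has no list, and the article gives no rule for choosing one. If the next entries on the two candidate lists differ, whoever picks the list picks the arm.

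**Block size.** With one known block size, a person who counts the allocations already made in a stratum can work out the last ones. Treatment is open and recruitment is in one department, so earlier allocations are visible in principle: under The Box, the article says that intervention patients receive their devices before discharge.

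At stake is selection at entry. The intervention relies on smartphone use, and the Generalizability section notes that smartphone literacy falls with age. A recruiter who foresees the next arm could approach or delay patients accordingly. The planned primary comparison is a chi-square test, with logistic regression only as a possibility if baseline imbalance is serious (Statistical Analyses). Selection on unmeasured traits such as motivation would pass straight into the primary result.

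**Working it through.** The article gives no figure of its own on this point, so there is none to reproduce. The inputs are its age classes, two diagnoses, block size 10, 1:1 ratio and 200 patients. Blocks are taken to run within each stratum, giving 2 × 5 = 10 strata.

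**1. Age classes.** Mapping every whole-year age from 18 to 100 to the five printed classes leaves exactly one age without a class, 50. No age falls in two classes. The share of patients aged 50 is not in the article. If it is assumed to be 1% to 3%, then 2 to 6 of 200 patients are affected.

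**2. Certain allocations in a complete block of 10.** There are C(10,5) = 252 equally likely sequences. The allocation at position *i* is certain when one arm has already used its five places, with probability 2 × C(*i*−1, 5) / 252:

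| Position | Probability certain |
|---|---|
| 1-5 | 0 |
| 6 | 2 × 1/252 = 0.8% |
| 7 | 2 × 6/252 = 4.8% |
| 8 | 2 × 21/252 = 16.7% |
| 9 | 2 × 56/252 = 44.4% |
| 10 | 2 × 126/252 = 100% |

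The sum is 2 × 210/252 = 1.67 per block, or 16.7%. This agrees with the general result 2m/(m+1) for a block of 2m: with m = 5, 10/6 = 1.67.

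**3. Best guessing.** The best rule is to guess the arm with more places left. Its expected number of correct guesses in a block of 2m is m + (4^m / C(2m, m) − 1)/2. For m = 5 this is 5 + (1024/252 − 1)/2 = 6.53 of 10, or 65%, against 50% by chance.

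**4. Whole trial.** If every block were completed, 200 × 0.167 = 33 allocations would be certain. In simulations of 200 patients over ten strata, about nine strata end in an incomplete block. About 27 of 200 (13%) are then certain, and about 64% can be guessed correctly. The article gives no stratum shares, so one equal and two assumed unequal mixes were tried; the results were nearly identical.

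**5. Alternative block sizes.** The formula in step 3 gives these expected correct guesses per block:

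| Block size | Correct guesses | Rate |
|---|---|---|
| 4 | 2.83 | 70.8% |
| 6 | 4.10 | 68.3% |
| 8 | 5.33 | 66.6% |
| 10 | 6.53 | 65.3% |
| 12 | 6 + (4096/924 − 1)/2 = 7.72 | 64.3% |

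- Equal mix of 4, 6 and 8: (2.83 + 4.10 + 5.33)/18 = 68.1%.
- Equal mix of 8, 10 and 12: (5.33 + 6.53 + 7.72)/30 = 65.3%.

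With incomplete blocks allowed for, simulation gives about 67% for 4/6/8 and about 64% for 8/10/12, the latter the same as for fixed blocks of 10. In a stratum of 20, fixed blocks of 10 leave about 17% of allocations certain. Either varying scheme leaves about 2%, even for an observer who knows the set of sizes but not their order.

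**The case against.** **The age gap looks like a slip.** The remaining classes suggest that the first was meant to include 50, and few patients are affected. Both points are fair. They make the fault small and the correction easy, but the rule as printed is still undefined for an eligible patient and nothing in the article settles it.

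**Foreseeing needs facts that the article does not give.** It does not say that recruiters know the block size, see all earlier allocations or keep a tally in each of ten strata. This stands as a limit: the figures above describe an observer who tallies without error. Nor can a reader infer that concealment is missing; a journal article commonly leaves that to the full protocol. What remains is a stated choice. The single size is published, and concealing the list does not hide allocations already made in an open trial.

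**Randomisation already follows inclusion.** This is correct, and it means that steering could act only through whom staff approach or include, and when. The Patient Population section allows inclusion up to 96 hours after primary PCI, so some room remains.

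**Fixed blocks of 10 are common and fairly large.** Also correct: smaller fixed blocks are worse, with 1.33 of 4 (33%) and 1.50 of 6 (25%) allocations certain. For the same reason, varying the size among small blocks would raise the best-guess rate.

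**Conclusion.** Both faults hold, each at minor-to-moderate weight, and they are independent of each other.

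- **Age 50:** a definite drafting fault that reaches only patients aged exactly 50.
- **Block size:** 1.67 of 10 allocations per complete block are certain, or about 27 of 200 (13%), for someone who tallies every stratum correctly. This rests on blocks running within strata, ten strata and incomplete last blocks; it is not sensitive to the stratum mixes tried.

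Three stronger readings are tempting but unsupported. The age gap does not make allocations predictable; only the fixed block size does. The figure of 33 certain allocations is an upper bound that needs every block to be completed. And the article gives no evidence that anyone foresaw or steered an allocation: the bias is possible, not shown.

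**What to change.** 1. State which stratum contains age 50, for example by defining the youngest class as 50 years or younger. For any 50-year-old already randomised, record which list was used.
2. From the next block in each stratum, use randomly varying block sizes that are not smaller on average than 10, such as 8, 10 and 12. Keep the sizes in a document that recruiting staff do not see. Avoid a mix such as 4, 6 and 8: it also cuts certain allocations to about 2%, but raises the best-guess rate to about 67-68%.

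The cost is one sentence of wording and regenerated lists. Balance within strata may be slightly looser: the largest possible imbalance inside an unfinished block is half its size, so it rises from 5 to 6 when a block of 12 is drawn. The best-guess rate stays at about 64-65%; the change removes nearly all certainty, not all predictability.

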### Patient Population

Patients who are admitted to the cardiology department of the LUMC with STEMI [1] or NST-ACS [2] will be eligible for participation. Patients with a STEMI or NST-ACS who match the inclusion and exclusion criteria will be approached for participation in the protocol within 24 hours after primary percutaneous coronary intervention (PCI). The maximum time between primary PCI and study inclusion is 96 hours. All inclusion and exclusion criteria are listed in Textbox 1.

Inclusion and exclusion criteria.Inclusion criteriaPatient is admitted with acute myocardial infarctionPatient is able to communicate in English or DutchExclusion criteriaBody Mass Index >35 kg/m^2^Included in another RCTDoes not have wireless Internet access at homeLess than 18 years oldConsidered an incapacitated adult (this decision is left to the discretion of the responsible cardiologist)PregnantUnwilling to sign the informed consent form

### Regular Follow-Up

Since 2004, the department of Cardiology of the LUMC has a dedicated care track for patients with STEMI or NST-ACS. Details about this protocol have been described previously by Liem et al [3]. Briefly, patients with signs and symptoms that are possibly related to a myocardial infarction are referred to a PCI center. Upon arrival, patients are immediately transferred to the catheterization department, where primary PCI of the culprit lesion is performed. Before discharge, patients are given written and oral information on the importance of medication adherence and lifestyle advices, in accordance with the European Guidelines on cardiovascular disease prevention in clinical practice [17].

After approximately 48-hours, patients are discharged from the hospital. The standard follow-up during the first year after discharge includes four outpatient clinic visits:

*Approximately 1 month after STEMI or NST-ACS*. This visit includes: a BP measurement; a 10-second, 12-lead ECG; laboratory testing (including kidney function, renal function, and lipid spectrum); and an interview with a doctor or nurse practitioner.*Approximately 3 months after STEMI or NST-ACS*. This visit includes: a BP measurement; a 10-second, 12-lead ECG; stress echo; a 24-hour Holter ECG, and an interview with a doctor or nurse practitioner.*Approximately 6 months after STEMI or NST-ACS*. This visit includes: a BP measurement, a 10-second, 12-lead ECG; a 24-hour Holter ECG; laboratory testing (including kidney function, renal function, and lipid spectrum); a transthoracic echocardiogram (TTE); and an interview with a doctor or nurse practitioner.*Approximately 12 months after STEMI or NST-ACS*. This visit includes: a BP measurement, a 10-second, 12-lead ECG; laboratory testing (including kidney function, renal function, and lipid spectrum); a TTE; and an interview with a doctor or nurse practitioner.

Patients who are randomized to regular follow-up receive the same care as patients who do not participate in the study. A flowchart of regular follow-up is detailed in Figure 1.

**Figure 1 figure1:**
[figure not shown]
MISSION, follow-up of patients who suffered from STEMI or NST-ACS. BP: blood pressure; ECG: electrocardiogram; NP: nurse practitioner; TTE: transthoracic echocardiogram.

**Figure 2 figure2:**
[figure not shown]
The Box.

### The Box

When randomized to *The Box* (Figure 2), patients will receive a box containing a weight scale, BP monitor, activity tracker, and a wearable ECG device. Patients will receive *The Box* before discharge and will be given the same written and oral information on the importance of medication adherence and lifestyle advices as the control group, in accordance with the European Guidelines on cardiovascular disease prevention in clinical practice [17]. The necessary apps will be downloaded on the patient’s smartphone; necessary accounts will be created and the installation of the devices will be carried out by a health care professional dedicated to the project. Afterwards, patients will be given oral instructions on the usage of the devices: they will be instructed to measure BP in a sitting position after five minutes of resting. The device should be applied to the left upper arm. Patients will be instructed to rest their left forearm on a table. Furthermore, a manual explaining the usage of the wearables (described below) will be handed over with *The Box*. Instruction videos are also available on YouTube. Patients who do not own a smartphone or tablet with iOS or Android OS but are willing to participate and be randomized to *The Box* will receive a smartphone. Patients will be instructed to use their own wireless Internet access (eg, home WiFi network). No mobile data network plan will be provided with the smartphone.

Patients will be instructed to record a single lead ECG, measure BP, and record their weight daily, preferably at the same time of day. Furthermore, participants will be asked to record a single lead ECG if any symptoms of possible cardiac origin occur (as interpreted by the patient). Lastly, patients will be instructed to wear their activity tracker during the day to track their daily number of steps, and at night to track the duration and quality of sleep. Patients will be told that measurements will be checked on a daily basis and that they will be contacted in cases of predefined data irregularities. Patients will be explicitly told that they cannot rely on the devices of *The Box* in emergency situations.

In addition to daily measurements, the first and third of the four standard outpatient clinic visits will be replaced by an electronic visit, in which the patient will communicate with the doctor or nurse practitioner via a secured video connection. The content of the interview will be comparable to the content of a regular outpatient clinic visit. The same doctors and nurse practitioners will perform the regular outpatient clinic visits and the digital outpatient clinic visits. In the intervention group, the 10-second 12-lead ECG and the laboratory testing one month after the index event will not be performed. Moreover, the 10-second 12-lead ECG, the 24-hour Holter ECG, laboratory testing, and the TTE 6 months after the index event will not be performed (Figure 1).

### Devices

All devices used for this study are noninvasive, battery powered, smartphone-compatible devices. All devices have a CE-mark, are approved by the United States FDA, and are allowed for over-the-counter sale in the European Union and the United States. The installation and usage of the devices are so intuitive that no medical staff needs to assist when the devices are used by the patient.

The usage of the devices requires a smartphone or tablet with Android Operating System (OS; Google, Mountain View, California, USA) or iOS (Apple Computers, Cupertino, CA, USA). The devices communicate with a dedicated mobile app on the smartphone or tablet, which can be downloaded from the App Store (iOS) or Play Store (Android). The data from the measurements are stored on the smartphone or tablet and uploaded to the app manufacturer’s servers (the cloud), which are located in Europe. An Internet connection (eg, WiFi, 3G, or 4G) is required to synchronize with the cloud. Measurements can be done while the smartphone or tablet is offline. In these cases, the results of the measurements are stored on the smartphone or tablet, and uploaded to the server when the smartphone is reconnected to the Internet.

#### Electrocardiogram Device

The ECG device (AliveCor, AliveCor Inc., San Francisco, CA, USA) contains two electrodes. The device communicates with the AliveCor app. The ECG device allows the user to record a 30-second single lead ECG. To record an ECG, the patient must position two or three fingers of the right hand on one electrode and two or three fingers of the left hand on the other electrode. The device is to be held within approximately 1 to 30 centimeters of the smartphone. An ultrasound signal is sent from the ECG device to the smartphone. This signal is then converted to a live single lead ECG that is subsequently shown on the smartphone screen [7,10].

After 30 seconds, an automated algorithm in the app calculates the R-R intervals and formulates a diagnosis, varying from *normal* to *possible atrial fibrillation* to *undetermined*, on the screen [10]. The patient then has the ability to add notes, and is requested to report any symptoms (if present) before saving the ECG.

